### Sample size calculation and statistical analysis

We will perform both Intention to Treat and Per Protocol analyses. We will conduct a sensitivity analysis [54], and compare complete cases versus cases lost to follow-up on baseline characteristics and scores on clinical measures, by randomization group [55]. Mixed Model Repeated Measures analyses will compare results on outcome measures across conditions and time points, while controlling for random effects (e.g. age, gender). Using medium effect sizes [56] 40 per group are required for power = .80 and α = .05 (G*Power) [57]. Recruiting an additional 20 % (*n* = 48 per group) will allow for typical dropout [58, 59]. Mechanisms of action (see Fig. 1), will be tested using multiple mediational analysis with 1000 bias-corrected bootstrap samples in MPlus, to test total and specific indirect effects. This powerful test of mediation requires a sample of 71 participants to detect a medium effect [60]. Participants will be classified into outcome categories (Recovered, Improved, Unchanged, Deteriorated) [61] according to Reliable Change Index and Clinical Significance of change at post-treatment and follow-up, to determine whether MBCT and ST differ in clinically significant reductions in NSSI and associated symptoms of anxiety and depression over time.

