### The current study

In this study we aim to: 1) determine the efficacy of group Mindfulness Based Cognitive Therapy (MBCT) in decreasing the frequency and medical severity of Non-Suicidal Self-Injury (NSSI) among young people, relative to group Supportive Therapy (ST); and 2) establish the mechanisms by which MBCT reduces frequency and severity of NSSI. The following hypotheses are proposed:We expect MBCT to reduce the frequency and medical severity of NSSI, relative to ST and this reduction to be maintained at 3 month and 6 month follow-upWe expect MBCT to increase mindfulness, reduce rumination, improve emotion regulation, improve distress tolerance, reduce bias for negative stimuli, and reduce stress (self-reported and physiological, based on cortisol)We expect the proposed mechanisms of action will mediate the relationship between assigned treatment group and outcomes of reduced NSSI, lower scores on the Beck Anxiety Inventory, and lower scores on the Beck Depression Inventory-II (Fig. 1).

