### Participants and recruitment

We will recruit 96 participants (48 per group) via our existing referral networks of GPs, mental health professionals, and university counselling services, as well as through advertising in print media and social network sites. Inclusion criteria include: 1) Aged 18–25 years, and 2) meet proposed DSM-5 criteria for NSSI [8]. Participants will be excluded if they: 1) are currently receiving psychological treatment, 2) have attempted suicide in the previous 12 months, 3) exhibit acute psychosis, 4) have a diagnosis of borderline personality disorder (BPD), or 5) have prior experience of MBCT. As NSSI is one diagnostic criterion for BPD, young people diagnosed with BPD will be excluded to avoid confounding diagnosis and behaviour. Individuals presenting with suicidal behaviour, psychosis or BPD will be appropriately referred.

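### Minor, nearly free improvement: 1000 bootstrap draws leave avoidable Monte Carlo error in borderline indirect effects; at least 10,000 would reduce it

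*Protocol article*

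**What the plan says.** The Protocol article, under Sample size calculation and statistical analysis, fixes both the method and the number of draws: "multiple mediational analysis with 1000 bias-corrected bootstrap samples in MPlus, to test total and specific indirect effects". It supports the analysis with a size statement, "This powerful test of mediation requires a sample of 71 participants to detect a medium effect", but gives no interval level and no rule for declaring a mechanism present. The only error rate in the section belongs to the group comparison ("40 per group are required for power = .80 and α = .05").

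The candidate mechanisms are in the hypotheses under The current study. MBCT is expected to "increase mindfulness, reduce rumination, improve emotion regulation, improve distress tolerance, reduce bias for negative stimuli, and reduce stress", with stress measured both by self-report and by cortisol. The mediated outcomes are "outcomes of reduced NSSI, lower scores on the Beck Anxiety Inventory, and lower scores on the Beck Depression Inventory-II". Establishing mechanisms is the second of the two stated aims. The Discussion describes the mechanism results as preliminary.

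**The concern.** A bootstrap limit is itself an estimate. With 1000 draws, each 2.5% tail rests on about 25 draws, and bias correction moves the cut-off further into one of the tails. A percentile estimated from so few draws varies between runs, and the estimated bias correction adds more variation. For an effect whose interval ends near zero, whether zero is excluded then depends partly on the seed.

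This error comes from the computation and not from the participants, so it can be reduced after the data are in. At stake is the list of mechanisms reported under the second aim: a re-run of the same data could name a slightly different set. The issue would affect any bootstrap interval built from 1000 draws and is separate from the choice of the bias-corrected type.

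**Working it through.** **The plan's own figure.** The article gives no Monte Carlo error or seed-stability figure, so there is none to reproduce on this point. The nearest is the 71 participants for mediation. A single-mediator, bias-corrected bootstrap simulation at N = 71 gives power of .54–.59 with both paths at .30, .77–.78 at .36 and .83–.85 at .39. So 71 would fit 80% power at paths of about .37. The article states neither path size nor power, so the figure is neither confirmed nor refuted.

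**Inputs from the article**
- Draws: B = 1000, bias-corrected.
- Sample: 96 recruited. With about 20% lost, 96 × 0.8 = 76.8; 76 was used.
- Mediators: 7, if self-reported stress and cortisol count separately.
- Outcomes: 3 (NSSI, BAI, BDI-II). This gives 7 × 3 = 21 specific effects, and 21 + 3 = 24 with the totals.

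**Assumptions.** A 95% interval; an effect is declared when the interval excludes zero; the count of effects as above (Fig. 1 is not shown).

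**Step 1: error of one tail.** SE = √(.025 × .975 / B).
- B = 1000: 0.0049, or about 0.5 percentage points. Two SEs either side put the effective tail at about 1.5% to 3.5%.
- B = 5000: 0.0022.
- B = 10,000: 0.0016.

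The bias-correction term has its own SE, √(.25/1000) / 0.399 = 0.040 at B = 1000.

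**Step 2: which effects are exposed.** For a normal bootstrap distribution, let q be the chance that one run excludes zero. Two seeds disagree with probability 2q(1 − q). For p = .06 and B = 1000, q = .246, so 2 × .246 × .754 = .371.

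| p with unlimited draws | B = 1000 | B = 5000 | B = 10,000 |
|---|---|---|---|
| .02 | 0.1% | 0% | 0% |
| .03 | 4% | 0% | 0% |
| .04 | 28% | 3.5% | 1.2% |
| .05 | 50% | 50% | 50% |
| .06 | 37% | 9% | 3% |
| .07 | 16% | 0.4% | 0% |
| .08 | 5% | 0% | 0% |
| .10 | 0% | 0% | 0% |

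More draws narrow the exposed band. They cannot settle an effect that lies exactly on the boundary.

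**Step 3: disagreement per effect.**
- One mediator, n = 80 or 96, treatment effect on the mediator 0–0.5 SD, mediator–outcome path 0.26–0.39: 2.3–5.2% at 1000 draws, 0.6–1.9% at 10,000.
- Seven mediators by three outcomes, N = 76 or 96, residual mediator correlation 0 or .4, medium, small or mixed effects: 3.0–5.3% at 1000.
- Same model, no effect on either path: 0.2–0.3% at 1000.
- One mediator with a very strong treatment effect on it (0.8 SD): 1–2% at 1000, under 0.5% at 10,000.

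**Step 4: at least one of the set.** Treating 21 effects as independent, 1 − (1 − .035)^21 = .53 at 1000 draws and 1 − (1 − .012)^21 = .22 at 10,000. Simulating the seven-mediator model avoids the independence assumption. With non-null effects and 1000 draws:
- any of 24 effects: 43–66% of trials;
- any of the seven NSSI mechanisms: 20–29%.

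With no mediation, any of 24 is 4–6%.

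**Step 5: what more draws buy.** N = 76, mediator correlation .4, medium treatment effects on the mediators and mixed mediator–outcome paths:

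| Draws | Per effect | Any of 24 | Any of 7 for NSSI |
|---|---|---|---|
| 1000 | 3.6% | 55% | 23% |
| 2000 | 2.6% | 43% | 17% |
| 5000 | 1.8% | 33% | 14% |
| 10,000 | 1.5% | 28% | 10% |

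Simulation error on the at-least-one figures is about 3–5 points. A second simulation of this setting gave 50% in place of 55% at 1000 draws.

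**The case against.** The strongest reply is that nothing here is stated wrongly. A thousand draws is an executable choice, each single conclusion is about 95–97% stable between seeds, and the unstable effects are those on which the data are already ambiguous. No systematic bias from the number of draws has been shown. All of that stands, and it limits the point to a minor one.

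A reader might also infer that the list of mechanisms will usually depend on the seed. The article does not support that without conditions. The excludes-zero rule, the 95% level and the count of 21–24 effects are all assumed, and the figure of about one half needs real medium or mixed effects. Much of it comes from counting many tests, which is why 28% remains at 10,000 draws.

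Comparing two runs also overstates the error of the one run that the trial will report. Against the conclusion from unlimited draws, a normal approximation multiplies the disagreement by 0.798 / 1.128 = 0.71. Then 3.5% becomes about 2.5% per effect, and 1 − (1 − .025)^21 = .41 replaces .53.

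A seed or a re-run rule may sit in an analysis plan that is not shown, and its absence from the article is no fault. A seed would make the result repeatable but would not reduce the error. What the reply does not remove is that the article itself fixes the number of draws, and a larger number costs almost nothing.

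**Conclusion.** The point holds as a minor improvement to a stated setting. Seed-dependence at 1000 draws is real but confined to effects with p of roughly .03 to .08. Its size is conditional: a few per cent per effect where the mediator relates to the outcome, and close to nothing where neither path exists. The figure of roughly half for the whole set applies only under the assumed decision rule, the assumed count and non-null effects.

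It would be wrong to read this as a flaw in the trial's main conclusion. Mediation serves the second aim, the article itself calls those results preliminary, and neither the primary comparison nor the planned recruitment depends on the number of draws.

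**What to change.** Replace 1000 with at least 10,000 bootstrap draws for every total and specific indirect effect. Where a limit lies within Monte Carlo error of zero, re-run with more draws before interpreting it, and report an effect that remains on the boundary as borderline. Record the seed so that the output can be reproduced.

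The cost is one number in the Mplus input and some computing time. The change can be made at any point before the analysis and needs no new data.

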## Discussion

Although delineated from suicidal behaviour by definition, people who repeatedly self-injure carry a fourfold risk of suicidal thoughts and behaviours within the following year [7], and are 42 times more likely to attempt suicide [2]. Of note, NSSI increases risk of suicidal behaviour over and above risk conferred by comorbid psychopathology, adverse life events and psychosocial risk factors [7, 62]. To reduce the physical, psychological, social and economic burden of self-injury, effective interventions are urgently needed [63]. MBCT is a transdiagnostic intervention that has established evidence in the treatment of many clinical conditions. Importantly, MBCT was designed specifically to focus on the very mechanisms thought to maintain self-injury (i.e. rumination, focus on negative thoughts, poor emotion regulation). MBCT thus offers untapped potential for reducing the frequency and medical severity of self-injury.

This trial offers significant advantages over previous efforts to determine effective treatments for NSSI. First, the components of MBCT directly align with cognitive and emotional factors related to NSSI, thus offering the best chance of targeting the key mechanisms maintaining the behaviour. Second, we will collect both self-report and clinician ratings of NSSI severity through the course of the project. These will be supplemented with behavioural measures of attentional bias and analysis of cortisol as a physiological measure of stress. These objective measures significantly strengthen the scientific rigour of the findings. Third, the active comparison condition allows additional control over the influence of group processes, therefore allowing a direct test of the specific intervention mechanism of MBCT.

While the proposed sample size is small, the repeated measures design ensures our study is sufficiently powered to identify medium effects on our primary outcome variable, and provide preliminary assessment of the mechanisms of change. Restricting our sample to 18–25 years necessarily will limit generalisation of the findings to other age groups, however given this is the age at which NSSI is most common [2] it seems the appropriate age range to first test the efficacy of MBCT in reducing this behaviour.

By directly addressing the mechanisms maintaining self-injury irrespective of psychiatric diagnosis, group mindfulness-based cognitive therapy (MBCT) offers great promise as a transdiagnostic treatment that can be a successful intervention for a greater number of young people who self-injure. Establishing efficacy of MBCT for self-injury will provide the first targeted evidence-based treatment, giving therapists the power to intervene confidently and produce positive outcomes for youth who self-injure [64]. Outcomes of this project will significantly improve the care given to those who self-injure, improve their well-being, decrease their chances of further self-injury, and decrease the chance they will die by suicide.

## Abbreviations

CAR: Cortisol awaking response
DS: Daily slope
DSM: Diagnostic and statistical manual of mental disorders
MBCT: Mindfulness based cognitive therapy
NSSI: Non-suicidal self-injury
ST: Supportive therapy
